However, LDCT screening focuses only on lung cancer, ignoring all other smoking related cancers (head and neck, esophagus, stomach, liver, colon, pancreas, kidney, bladder, ovary, uterine cervix and myeloid leukemia) [14]. On the other hand, strong concerns have been raised about possible harmful consequences of screening: false positive results requiring repeated and potential invasive procedures among participants without cancer, theoretical risk of radiation – induced carcinoma, and a poorly known psychological impact of screening procedures [15]. Screening should thus be applied to a population at high risk of smoking induced cancer.

Presence of circulating tumor cells (CTC) is considered as a sensitive biomarker for early metastatic cascade, cancer progression and drug treatment monitoring [16]. The Isolation by Size of Epithelial Tumor cells (ISET) technology is a blood filtration-based approach that has the potential to detect circulating non-hematologic cells [17]. Clinical data highlighted that these cells can be isolated in the blood stream before cancer was detectable on imaging [18].

In order to address not only lung cancer but all tobacco-related cancers in smokers and ex-smokers suffering from atherosclerotic PAD and/or AAA, the DETECTOR study will analyze the interest of CTC detection associated with LDCT for an early detection of cancers associated with PAD. The psychological part of the study will focus on emotional and psychosocial impact on participants of this screening strategy, and particularly those psychosocial mechanisms involved in the search of CTC. The psychological research team will also assess physician communication strategies.

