### Objectives

The primary objective of the study is to determine the diagnostic value of the couple LDCT combined with CTC search for the early detection of smoking associated cancers in a cohort of asymptomatic but high-risk participants presenting with PAD and/or AAA.

The secondary objectives are (1) to describe detected malignancies with this screening strategy and to evaluate patient’s survival, (2) to evaluate the rate of detection of CTCs in the study population, (3) to study the effect of smoking cessation program on patient’s decision to quit smoking, (4) to study the emotional and psychosocial impact of this screening strategy and more specifically related to CTC detection, (5) to assess, adjust and improve communication strategies of health professionals.

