### Management of incidental findings

First-line screening incidental findings and adapted screening strategy are displayed in Table 2. In case of negative LDCT or incidental lung nodule(s) with a volume < 50 mm^3^ and absence of CTCs, this screening strategy will be repeated once a year for a total of 3 consecutive rounds. Participants will be excluded from further screening when diagnosed with lung cancer or extra-pulmonary malignancy. In case of incidental lung nodule(s) with a volume > 500 mm^3^, in the presence or absence of CTCs, a specific multidisciplinary team meeting will discuss diagnostic and pre-therapeutic evaluation for lung cancer [23]. In case of incidental lung nodule(s) with a volume between 50 and 500 mm^3^ and presence of CTCs, diagnostic and pre-therapeutic evaluation for lung cancer will also be performed. In the absence of CTCs, volume doubling time - evaluated through a second LDCT performed three months later - will be taken into consideration for adapted diagnostic management. In case of negative LDCT or incidental lung nodule(s) with a volume < 50 mm^3^, and presence of CTCs, a contrast enhanced whole-body scanner and PET/CT associated with clinical head and neck examination and cytological examination of the urine will be performed for extra-pulmonary malignancy screening and management (Fig. 1).

**Table 2 Tab2:** First-line screening incidental findings and adapted screening strategy

Low –dose chest CT and search for CTCs	No incidental lung nodule or nodule(s) <50mm^3^	Incidental lung nodule(s) with volume between 50 and 500mm^3^	Nodule(s) >500mm^3^
No CTC	Next screening round at one year	Measure of volume doubling time at low-dose chest CT 3 months later	Diagnostic and pretherapeutic evaluation
Presence of CTC	Contrast enhanced whole-body scanner and PET/CT examination of the head and neck cytological examination of the urine	Diagnostic and pretherapeutic evaluation	Diagnostic and pretherapeutic evaluation

*CTC: circulating tumor cells; PET/CT: Positron emission tomography-computed tomography*

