### Statistical analysis and sample size

Data will be analyzed using SAS and R software. Alpha level for statistical significance (p) will be set at less than 5%. Characteristics of the study population will be described as mean plus or minus standard deviation for continuous variables with a normal distribution and as median [interquartile range] for skewness distribution. Categorical variables will be described as numbers and proportions. Student’s t-test or nonparametric Wilcoxon test will be used to compare quantitative parameters between different groups of patients and Chi2 test or Fischer test for qualitative parameters.

The primary outcome will focus on the sensibility and specificity of the screening strategy associating detection of CTCs and LDCT. Statistical analysis is in accordance with the STARD (Standards for Reporting of Diagnostic Accuracy Studies) guidelines [24]. To meet the primary objective, sensitivity will be estimated by dividing the number of patients diagnosed by the CTC method by the number of patients with lung cancer confirmed by the reference technique, i.e. LDCT. The results will be expressed with a binomial proportion 95% confidence interval. Specificity will be estimated by dividing the number of patients diagnosed with CTC as cancer-free with the number of patients without lung cancer. Secondary evaluation criteria will be analyzed using the same statistical methods as those used for the primary endpoint.

Assuming 10% prevalence of smoking-associated cancer in the studied population [8], if we aim to study a total of at least 30 detected cancers, including baseline and repeat screening rounds, we need to enroll a total of at least 300 participants.

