Different CTC isolation/detection methods exist. Transition of epithelial differentiation to mesenchymal phenotype is an important biological process leading to the generation of more aggressive sub-populations of CTCs. These invasive CTCs may not be captured with isolation/detection methods considering epithelial-lineage or tissue markers leading to false negative results, especially in patients with lung cancer [36]. The DETECTOR study will be the first prospective study analyzing the interest of CTC search with ISET technique in association with LDCT, possibly supplemented by whole-body imaging, in the screening strategy of smoking-associated cancers in PAD patients. A main challenge of the study is the detection method of CTCs, considering their low abundance in peripheral blood, fragility, heterogeneity and the lack of organ-specific markers [37]. If positive this study could pave the way for other cardiovascular population with a history of smoking, such as patients with coronary artery disease.

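### CTC specificity is computed over everyone without lung cancer, so every confirmed non-lung malignancy is scored as a non-case, against the objective and the work-up

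*Protocol article*

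**What the plan says.** The Protocol article uses three different notions of a cancer case.

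- **Objectives.** The study is to determine "the diagnostic value of the couple LDCT combined with CTC search for the early detection of smoking associated cancers". The Background names the sites other than lung: "head and neck, esophagus, stomach, liver, colon, pancreas, kidney, bladder, ovary, uterine cervix and myeloid leukemia". The sample size in Statistical analysis and sample size is also built on smoking-associated cancer.
- **Management of incidental findings.** "Participants will be excluded from further screening when diagnosed with lung cancer or extra-pulmonary malignancy". Neither this rule nor the work-up is limited to smoking-related sites. The work-up is whole-body scanner and PET/CT, head and neck examination and urine cytology after a positive CTC result with a negative LDCT or nodules below 50 mm³.
- **Statistical analysis and sample size.** "The primary outcome will focus on the sensibility and specificity of the screening strategy associating detection of CTCs and LDCT". The formulas then use lung cancer only. Sensitivity is taken over "the number of patients with lung cancer confirmed by the reference technique, i.e. LDCT". For specificity: "Specificity will be estimated by dividing the number of patients diagnosed with CTC as cancer-free with the number of patients without lung cancer".

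The Discussion adds that CTCs carry no organ-specific markers, and Inclusion and screening procedures defines positivity by malignant cytology, not by site. No section says how a confirmed malignancy outside the lung, or outside the Background list, is classified in the accuracy analysis.

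**The concern.** A specificity whose denominator is everyone without lung cancer treats each confirmed non-lung malignancy as absence of disease. If the CTC test was positive, that participant counts as a false positive, although the cytology was right and the work-up found the tumour it was meant to find. If the CTC test was negative, the participant counts as a true negative, although a cancer was missed.

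Most of those affected would be people with bladder, pancreatic, head and neck or other listed cancers, the very cancers that justify adding CTC search to LDCT. The Discussion expects CTC detection to reduce the false positives of conventional imaging, so what counts as a CTC false positive bears directly on a stated aim.

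The obvious repair, putting smoking-associated cancer in place of lung cancer, leaves a smaller gap. A test without organ-specific markers, followed by whole-body imaging, can lead to a cancer that is not on the list (prostate or breast, for example). That person would still be scored as cancer-free.

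**Working it through.** **The plan's own figure.** Target number of cancers ÷ prevalence = 30 / 0.10 = 300, which matches the stated minimum enrolment. This figure is not in dispute. It implies 300 − 30 = 270 participants without smoking-associated cancer.

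**Assumptions, because the documents give no figures:** CTC specificity in people with no cancer, sp = 95%; CTC sensitivity for any cancer, s = 50% to 80%; 10 to 20 of the 30 cancers are lung cancers; a small number k of cancers lie outside the Background list.

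**Step 1: the formula as written (target lung cancer).** Let e be the number of smoking-associated extra-pulmonary cancers, with no off-list cancers. The denominator is 270 + e.

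Scored specificity = [0.95 × 270 + (1 − s) × e] / (270 + e)

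| e | s | Counted as false positive | Counted as true negative | Scored specificity |
|---|---|---|---|---|
| 10 | 50% | 5 | 5 | 261.5/280 = 93.4% |
| 10 | 80% | 8 | 2 | 258.5/280 = 92.3% |
| 20 | 50% | 10 | 10 | 266.5/290 = 91.9% |
| 20 | 80% | 16 | 4 | 260.5/290 = 89.8% |

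Against 95% in the cancer-free, the loss is 1.6 to 5.2 points.

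**Step 2: after widening the target to smoking-associated cancer.** Only the k off-list cancers remain among the 270.

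Scored specificity = [0.95 × (270 − k) + (1 − s) × k] / 270

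- k = 3: 255.15/270 = 94.5% (s = 50%) to 254.25/270 = 94.2% (s = 80%)
- k = 6: 253.8/270 = 94.0% to 252/270 = 93.3%
- k = 15: 92.5% to 90.8%

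For k = 3 to 6 the loss is 0.5 to 1.7 points.

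**Step 3: the same residue with fixed counts.** Assume 10 CTC-positives with no malignancy and k CTC-positives with an off-list cancer. Compare (260 − k)/270, target smoking-associated cancer, with (260 − k)/(270 − k), target any malignancy.

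- k = 3: 257/270 = 95.2% against 257/267 = 96.3%, a difference of 1.1 points
- k = 6: 254/270 = 94.1% against 254/264 = 96.2%, a difference of 2.1 points

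The 95% half-width of the first estimate (normal approximation) is 1.96 × √(0.952 × 0.048 / 270) ≈ 2.5 points at k = 3 and about 2.8 points at k = 6. The residual shift is smaller than sampling error.

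**Direction.** In Step 2 the change in specificity is k × (1 − s − 0.95)/270. It is downward whenever s exceeds 5%, so under any plausible CTC sensitivity the scoring understates specificity. The missed cancers counted as true negatives offset part of that loss and are not identified in the ratio.

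**The case against.** Several objections have force.

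- **Off-target cancers are non-cases by definition.** Specificity for smoking-associated cancer is properly calculated over everyone without it; any malignancy is a different target. This stands, and it is why the off-list part is a matter for a supporting analysis. It does not excuse the lung-only denominator, which departs from the declared objective.
- **The stopping rule is not a scoring rule.** A reader might infer from the end-of-screening sentence that off-list cancers are scored wrongly there. It does not support that: stopping screening on any cancer is compatible with a narrower accuracy target. The scoring follows from the specificity formula.
- **Classification may be in the full protocol or the analysis plan.** That could be so for off-list cancers. The formula, however, is printed, and it conflicts with the objective in the same article.
- **Other cancers would still be reported.** A secondary objective is to describe the detected malignancies, without site restriction. So they would not be hidden, though that description does not alter the accuracy ratio.
- **Predictive value.** A reader might look to it for a larger effect. The article names only sensitivity and specificity as the primary outcome, so a shift in predictive value is not a shift in a planned result.
- **Removing other cancers from the denominator is tempting but unsound.** Scheduled whole-body imaging follows only a positive CTC result, so confirmed other cancers will be mostly CTC-positive. Removing them would chiefly delete false positives, leave undetected CTC-negative cancers in place, and inflate specificity.

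**Conclusion.** The point holds against the specificity formula. Followed exactly, it scores every confirmed non-lung malignancy as a non-case, which conflicts with the objective and with the purpose of the work-up. Under the stated assumptions this costs 1.6 to 5.2 points of specificity from listed extra-pulmonary cancers alone.

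A reader might infer that the written analysis already targets smoking-associated cancer, so that only off-list cancers are misplaced. The documents do not support this: the objective and the sample size use that target, while both accuracy formulas use lung cancer.

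The part that survives widening the target is probably small, about 1 to 2 points for 3 to 6 off-list cases among 270. The number of such cases, the 95% specificity and the 50 to 80% sensitivity are all assumed. Exclusion at entry of recent cancer and of signs suggestive of malignancy would keep the number down. The correction is worth making because it is cheap and settles what a CTC false positive means, not because the residual bias is large.

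**What to change.** In Statistical analysis and sample size:

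1. Use smoking-associated cancer (lung plus the Background list) as the target condition for both sensitivity and specificity. LDCT cannot confirm extra-pulmonary disease, so case status has to come from the diagnostic work-up and follow-up.
2. Classify each confirmed malignancy as smoking-associated or other.
3. Keep participants with another malignancy in the primary specificity denominator, and show them as a separate row by CTC result.
4. Pre-specify a supporting analysis with any newly diagnosed malignancy, non-melanoma skin cancer excepted, as the target.
5. State that other cancers will be found preferentially in CTC-positive participants, because scheduled whole-body imaging follows only a positive CTC result, and that the supporting estimate is therefore subject to partial verification.

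The cost is wording, one table and one further estimate to report and explain. Tumour site should already be available from the work-up. No clinical procedure changes.

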**Fig. 1 Fig1:**
[figure not shown]
Adapted screening strategy in case of negative low-dose chest CT or incidental lung nodule(s) with a volume < 50 mm^3^ and presence of circulating tumor cells (CTCs)

### Collection of data

The usual demographic data will be recorded, including gender, age, weight, height, history of dyslipidemia, diabetes, hypertension, smoking habits, previous diseases and use of medications. History of coronary heart disease and cerebro-vascular disease will be recorded. For PAD, clinical and hemodynamic evaluations (ankle-brachial or toe-brachial index) will provide insights on the ischemia severity. All clinical, biological and imaging data will be anonymized and stored in electronic format.

### Statistical analysis and sample size

Data will be analyzed using SAS and R software. Alpha level for statistical significance (p) will be set at less than 5%. Characteristics of the study population will be described as mean plus or minus standard deviation for continuous variables with a normal distribution and as median [interquartile range] for skewness distribution. Categorical variables will be described as numbers and proportions. Student’s t-test or nonparametric Wilcoxon test will be used to compare quantitative parameters between different groups of patients and Chi2 test or Fischer test for qualitative parameters.

The primary outcome will focus on the sensibility and specificity of the screening strategy associating detection of CTCs and LDCT. Statistical analysis is in accordance with the STARD (Standards for Reporting of Diagnostic Accuracy Studies) guidelines [24]. To meet the primary objective, sensitivity will be estimated by dividing the number of patients diagnosed by the CTC method by the number of patients with lung cancer confirmed by the reference technique, i.e. LDCT. The results will be expressed with a binomial proportion 95% confidence interval. Specificity will be estimated by dividing the number of patients diagnosed with CTC as cancer-free with the number of patients without lung cancer. Secondary evaluation criteria will be analyzed using the same statistical methods as those used for the primary endpoint.

Assuming 10% prevalence of smoking-associated cancer in the studied population [8], if we aim to study a total of at least 30 detected cancers, including baseline and repeat screening rounds, we need to enroll a total of at least 300 participants.

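### The primary sensitivity and specificity are computed from the CTC result alone and for lung cancer only, so neither is the accuracy of the combined CTC and LDCT strategy for smoking-associated cancers

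*Protocol article*

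**What the plan says.** In the protocol article, the Objectives section sets the primary aim: "to determine the diagnostic value of the couple LDCT combined with CTC search for the early detection of smoking associated cancers". The section on statistical analysis and sample size repeats the combined strategy as the endpoint: "The primary outcome will focus on the sensibility and specificity of the screening strategy associating detection of CTCs and LDCT". The sample size in that section also counts smoking-associated cancers.

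The same section then gives the formulas meant to serve the primary objective. For sensitivity: "sensitivity will be estimated by dividing the number of patients diagnosed by the CTC method by the number of patients with lung cancer", where the denominator is "the number of patients with lung cancer confirmed by the reference technique, i.e. LDCT". For specificity: "Specificity will be estimated by dividing the number of patients diagnosed with CTC as cancer-free with the number of patients without lung cancer".

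The section on management of incidental findings (with Table 2) shows that LDCT triggers work-up by itself. A nodule evaluation follows "In case of incidental lung nodule(s) with a volume > 500 mm^3^, in the presence or absence of CTCs". For nodules of 50 to 500 mm³ the rule is: "In the absence of CTCs, volume doubling time - evaluated through a second LDCT performed three months later - will be taken into consideration". A CTC-positive participant with no nodule, or one below 50 mm³, goes to whole-body imaging, head and neck examination and urine cytology, which "will be performed for extra-pulmonary malignancy screening and management".

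No other section gives a formula for the combined strategy or for all smoking-associated cancers.

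**The concern.** The stated test is CTC plus LDCT and the stated disease is any smoking-associated cancer. In both formulas the test is CTC alone and the disease is lung cancer alone. Four consequences follow.

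- **Nodule-driven false positives vanish.** A cancer-free, CTC-negative participant sent to evaluation for a nodule is scored as a correct negative. The Background names unnecessary and possibly invasive follow-up as a main harm of screening, and the Discussion expects CTC testing to reduce imaging false positives. The printed specificity cannot show either.
- **Correct extra-pulmonary detections count as errors.** A CTC-positive participant with an extra-pulmonary cancer is without lung cancer, so is scored as a false positive, although the whole-body work-up exists to find that person.
- **Sensitivity gives LDCT no credit and omits part of the target.** A CTC-negative lung cancer found by LDCT is a miss, and extra-pulmonary cancers are not in the denominator.
- **The reference is half of the test.** A lung cancer that LDCT misses cannot be counted.

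Both primary results would be read as the accuracy of the strategy, and neither would be.

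**Working it through.** **Stated figure.** 30 cancers / 0.10 prevalence = 300 participants. This reproduces the protocol's sample size. The 30 are smoking-associated cancers, so the printed sensitivity denominator holds only the lung cancers among them.

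**Inputs.** From the protocol: N = 300, 30 cancers, hence 270 participants free of smoking-associated cancer. Assumed, because the documents give no rates:
- c: CTC false-positive rate
- w: share of CTC-negative, cancer-free participants evaluated because of a nodule (above 500 mm³, or 50 to 500 mm³ with a doubling time that leads to evaluation)
- E: number of extra-pulmonary cancers; p: CTC positivity in them
- s: CTC positivity in lung cancers
- v: share of CTC-negative lung cancers flagged by a nodule

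I take one overall result per participant and cancer status as settled by work-up and follow-up. Each numerator is read as a subset of its denominator.

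**Specificity.**
- CTC alone, in the 270: 1 − c
- Strategy, in the 270: (1 − c)(1 − w), which can never exceed 1 − c
- As printed: [270(1 − c) + E(1 − p)] / (270 + E)

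With c = 0.05, CTC alone gives 95.0% and 256.5 CTC-negatives. With E = 15 and p = 0.8, the printed figure is (256.5 + 3)/285 = 259.5/285 = 91.05%.

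| w | nodule evaluations, 256.5 × w | strategy | printed minus strategy |
|---|---|---|---|
| 2% | 5.1 | 93.1% | −2.0 points |
| 5% | 12.8 | 90.25% | +0.8 |
| 10% | 25.7 | 85.5% | +5.6 |

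The sign changes at w = 1 − 0.9105/0.95 = 4.2%. Other mixes at c = 0.05:
- E = 10, p = 0.5: 261.5/280 = 93.4%, sign change at w = 1.7%
- E = 20, p = 0.8: 260.5/290 = 89.8%, sign change at w = 5.4%

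With E = 15, p = 0.8 and w from 2% to 10%, the difference runs from −2.1 to +5.7 points at c = 0.02 (printed 267.6/285 = 93.9%) and from −1.9 to +5.3 at c = 0.10 (printed 246/285 = 86.3%).

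**Sensitivity.** Take 15 lung and 15 extra-pulmonary cancers, assume nodules find no extra-pulmonary cancer, and take s as the same whether or not LDCT confirms the cancer.
- As printed, numerator limited to lung cancers: s
- Strategy: {15[s + (1 − s)v] + 15p}/30

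Results:
- s = 0.5, v = 0.8, p = 0.8: printed 50%; strategy (13.5 + 12)/30 = 85%
- s = 0.8, v = 0.8, p = 0.5: printed 80%; strategy (14.4 + 7.5)/30 = 73%
- Lung cancers alone, strategy: 0.5 + 0.5 × 0.8 = 90% and 0.8 + 0.2 × 0.8 = 96%, against 50% and 80%

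Read literally, the numerator is not limited to lung cancers. In the first case it is 7.5 + 12 = 19.5, and 19.5/15 = 130%, which is not a proportion.

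**Reference.** If lung cancer is whatever LDCT confirms, every diseased participant is LDCT-positive and therefore strategy-positive. Putting the combined result into the printed formula gives 100% by construction. The test result and the reference must change together.

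**The case against.** - **Left to a fuller document.** This does not apply. The article prints the formulas, and they contradict its own primary outcome.
- **The formulas are a legitimate component comparison of CTC with LDCT.** That is a fair reading of their use, and CTC-only accuracy is worth reporting. It then should not carry the label of the strategy's accuracy, and the reading does not rescue the lung-only denominator. The secondary objectives describe all detected malignancies and the CTC detection rate, so extra-pulmonary cancers would be reported, but not within the primary result.
- **The sizes rest on assumed rates and show no direction.** This stands. The figures illustrate; the argument is the mismatch of definitions. The sensitivity comparison also depends on limiting the numerator to lung cancers, but the literal reading serves the plan worse.
- **A replacement has loose ends.** This partly stands. No doubling-time threshold is printed, three annual rounds need a stated unit of analysis, and participants negative on both tests get no whole-body work-up, so their extra-pulmonary cancers surface only through later rounds and follow-up. Table 1 also shows no contact after five weeks past the second annual visit, although the text promises at least 3 years of follow-up. That reference is imperfect, but LDCT cannot establish extra-pulmonary status at all.

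**Conclusion.** The concern holds. Followed as written, the plan yields neither the sensitivity nor the specificity of the strategy it names as its primary outcome. That conclusion rests on the text alone.

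Under the assumed rates, the printed specificity lies between about 2 points below and nearly 6 points above the strategy's. The printed sensitivity is 35 points too low in one scenario and 7 points too high in the other. No single direction of bias can be claimed. It depends on the extra-pulmonary share, CTC positivity by site and the rate of nodule-driven evaluation. The sample size of 300 is unaffected.

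**What to change.** 1. Define strategy-positive from Table 2: CTC present, or a nodule above 500 mm³, or a 50 to 500 mm³ nodule whose doubling time leads to evaluation. Use it for both measures, and state whether it is counted per participant across the rounds or per round.
2. Replace LDCT as the reference with confirmed smoking-associated cancer by the end of follow-up. Compute sensitivity over all participants with such a cancer and specificity over all without.
3. As a check on the missing doubling-time threshold, also report specificity with the whole CTC-negative, 50 to 500 mm³ repeat-LDCT group counted as negative and then as positive.
4. Keep CTC-only sensitivity and specificity as component measures, labelled as such.
5. Tabulate work-ups in cancer-free participants by trigger (CTC or nodule), with exact 95% confidence intervals.

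The cost is a change of definitions and one table. It uses the clinical, biological and imaging data the protocol already stores, the planned work-ups and the stated follow-up of at least 3 years, with no test or visit beyond those. The downsides are some coding of work-up records, final figures only after follow-up ends, incomplete verification of participants negative on both tests, and a possibly less favourable specificity.

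### The primary formulas take lung cancer as the target condition although the objective is all smoking-associated cancers, so extra-pulmonary cancers found through CTC count against specificity and the sensitivity ratio is incoherent

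*Protocol article*

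**What the plan says.** Under Objectives, the primary aim is to determine "the diagnostic value of the couple LDCT combined with CTC search for the early detection of smoking associated cancers". The Background gives the reason for adding CTC: it states that "LDCT screening focuses only on lung cancer, ignoring all other smoking related cancers", lists those other cancers, and introduces the study with the words "In order to address not only lung cancer but all tobacco-related cancers in smokers and ex-smokers".

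Management of incidental findings and Table 2 follow that aim. If CTCs are present and LDCT is negative or shows only nodules below 50 mm³, whole-body imaging, a head and neck examination and urine cytology "will be performed for extra-pulmonary malignancy screening and management". If CTCs are absent and LDCT shows the same, the patient waits for the next yearly round.

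Statistical analysis and sample size names the primary outcome as the "sensibility and specificity of the screening strategy associating detection of CTCs and LDCT". It then gives two formulas meant to serve the primary objective:

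- Sensitivity: "dividing the number of patients diagnosed by the CTC method" by the number with lung cancer confirmed by LDCT, which is called the reference technique.
- Specificity: "dividing the number of patients diagnosed with CTC as cancer-free with the number of patients without lung cancer".

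The same section bases the sample size on a 10% prevalence of smoking-associated cancer and at least 30 detected cancers.

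**The concern.** The target condition changes between the objective and the formulas. A patient with bladder cancer and no lung cancer belongs, under the written rule, among the patients without the disease. The detections for which CTC was added then lower the reported specificity. The sensitivity denominator leaves these patients out, while its numerator is not limited in the same way.

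The primary result would thus answer a different question from the primary objective. The 30 cancers that justify 300 participants would also not be the denominator of the planned sensitivity.

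**Working it through.** **Sample size.** 30 cancers / 0.10 = 300, so the plan's figure reproduces. It counts all smoking-associated cancers, which gives 30 diseased and 270 non-diseased participants.

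**Where each patient falls under the written specificity formula**

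- No cancer, CTC-negative: numerator and denominator, a true negative.
- No cancer, CTC-positive: denominator only, a false positive.
- Extra-pulmonary cancer only, CTC-positive: denominator only, a false positive.
- Extra-pulmonary cancer only, CTC-negative: numerator and denominator, a true negative, even if the cancer is known by the time of analysis.

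**Perfect CTC test.** Suppose all 30 cancers are CTC-positive and all 270 cancer-free participants are CTC-negative. The article does not give the number of lung cancers L, so 10 to 25 is assumed. Written specificity = 270 / (300 − L).

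| Lung | Extra-pulmonary | Written specificity | Specificity, all-cancer target |
|---|---|---|---|
| 10 | 20 | 270/290 = 93.1% | 270/270 = 100% |
| 15 | 15 | 270/285 = 94.7% | 100% |
| 20 | 10 | 270/280 = 96.4% | 100% |
| 25 | 5 | 270/275 = 98.2% | 100% |

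With 15 extra-pulmonary cancers, a test that missed all of them but was otherwise perfect would score (270 + 15)/285 = 100%. On this measure it would beat the perfect test.

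**Imperfect CTC test.** Assume 15 lung and 15 extra-pulmonary cancers, and a true specificity of 95% among the cancer-free (270 × 0.95 = 256.5 negatives).

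- CTC sensitivity 80%: 12 found extra-pulmonary cancers become false positives, so 13.5 + 12 = 25.5 in all, and 3 missed ones become true negatives. Specificity = (256.5 + 3)/285 = 91.1%.
- CTC sensitivity 60%: 9 become false positives and 6 become true negatives. Specificity = (256.5 + 6)/285 = 92.1%.

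Over 10 to 25 lung cancers, CTC sensitivity of 60% to 100% and true specificity of 90% to 95%, the loss runs from 0.9 to 6.6 percentage points. These illustrations treat the 30 as all cancers present, although the article speaks of detected cancers.

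**Sensitivity.** Read literally, with 80% of all 30 cancers CTC-positive and 15 lung cancers, the ratio is 24/15 = 1.6. If the numerator is silently limited to lung cancer, it is 12/15 = 80%, but on half the intended base. The exact 95% interval is then 52% to 96%, against 61% to 92% for 24/30.

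**The case against.** The best defence of a lung-only target is that every participant has LDCT at each round, so lung cancer is looked for in everyone. The extra-pulmonary search is given only to CTC-positive patients with a negative LDCT or nodules below 50 mm³. An all-cancer target therefore brings in partial verification. In the example above, if the 3 missed extra-pulmonary cancers never surfaced, observed extra-pulmonary sensitivity would be 12/12 = 100% instead of 12/15 = 80%. This objection stands as a limit on the remedy. It does not justify formulas that contradict the objective, and the article neither gives it as a reason nor defines another primary accuracy analysis.

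Three stronger readings are tempting and are not supported:

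- *Sensitivity gives extra-pulmonary detections no credit.* The numerator is not limited to lung cancer, so a literal reading counts them and inflates the ratio. The bias against CTC is established for specificity only. For sensitivity the formula is incoherent and has no settled direction.
- *Undetected extra-pulmonary cancers become true negatives because of the lung-only denominator.* A cancer that is never detected is a true negative under any target definition. The denominator matters only for missed cancers that later become known.
- *Rewording the two formulas is enough.* Rewording alone would leave extra-pulmonary ascertainment dependent on CTC status.

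The sizes are also illustrative, because the lung share and CTC accuracy are assumptions.

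**Conclusion.** The formulas are wrong as written. Their target condition contradicts the primary objective, the CTC-triggered work-up and the sample size, and nothing elsewhere in the article repairs this. This is not a matter of detail left to a fuller document, since the formulas are stated and name the wrong condition.

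The misclassification follows from the wording alone; only its size rests on assumptions. The perfect-test result needs just the assumed lung share, whereas the readings of about 91% to 92% also need the assumed 95% specificity and 60% to 80% CTC sensitivity. The total of 300 is not itself in error. The formulas should be corrected before the primary analysis.

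**What to change.** 1. In both formulas, define the target condition as any smoking-associated cancer on the Background list.
2. Name the reference standard: cancer confirmed by the diagnostic work-up, or by the cancer-focused clinical events already collected at V1 and V2 (Table 1) and during the follow-up of at least 3 years (Study design). LDCT alone should not serve as the reference.
3. State which LDCT and CTC results count as positive for the combined strategy. One case to settle for the analysis is a nodule of 50 to 500 mm³ without CTCs, whose result awaits the three-month LDCT.
4. Compute sensitivity as strategy-positive patients with such a cancer over all patients with such a cancer, and specificity as strategy-negative patients without one over all patients without one.
5. Report lung and extra-pulmonary cancers as separate subsets, with patients free of any smoking-associated cancer as the common specificity denominator.
6. State that extra-pulmonary cancers in CTC-negative patients are ascertained only through follow-up, so extra-pulmonary sensitivity may be overestimated.

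The cost is a rewritten paragraph with a reference-standard and a positivity definition. The sample size stays at 300 and no visit or examination is added. The price is the partial verification in item 6, which the planned follow-up reduces but does not remove.
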